## Abstract

**Background:**

Locally advanced cervical cancer (LACC) remains a major global health burden, and current imaging-based assessment after standard concurrent chemoradiotherapy (CCRT) is limited by delayed detection of treatment failure and poor sensitivity for microscopic residual disease. Circulating human papillomavirus DNA (HPV ctDNA) represents a tumor-specific biomarker with potential for real-time treatment monitoring. This prospective cohort study aims to evaluate whether dynamic monitoring of plasma HPV ctDNA can predict treatment response and prognosis in patients with LACC receiving CCRT.

**Methods/design:**

This single-center, observational cohort study will enroll 57 patients with histologically confirmed LACC (FIGO 2018 stage IB2–IVA) and baseline high-risk HPV infection. All patients will receive standard CCRT including external beam radiotherapy (45–50.4 Gy), concurrent weekly cisplatin (40 mg/m²), and intracavitary brachytherapy. Peripheral blood samples (10 mL) will be collected at five predefined time points: baseline (T0), mid-treatment (T1), end of CCRT (T2), 3 months post-CCRT (T3), and every 6 months thereafter for 24 months. Plasma HPV ctDNA will be quantified using droplet digital PCR targeting HPV16/18 E6/E7 genes. The primary endpoint is progression-free survival (PFS), comparing patients with detectable versus undetectable ctDNA at 3 months post-CCRT.

**Conclusion:**

This study will provide prospective evidence for HPV ctDNA as a minimally invasive biomarker for treatment monitoring and prognostic stratification in LACC, potentially informing future risk-adapted therapeutic strategies.

## Introduction

Cervical cancer remains a substantial global health challenge, with an estimated 662,044 new cases and 348,709 deaths occurring worldwide in 2022, representing the fourth most common malignancy and cause of cancer-related mortality in women (1). The burden disproportionately affects low- and middle-income countries, where 90% of cervical cancer deaths occur, primarily reflecting inequities in access to human papillomavirus (HPV) vaccination, screening programs, and definitive treatment services (2). Notably, China and India together account for 42% of global incident cases and 39% of deaths, with projections indicating a 56.8% increase in new cases and an 80.7% rise in mortality by 2050 if current rates remain unchanged (1).

Locally advanced cervical cancer (LACC), encompassing International Federation of Gynecology and Obstetrics (FIGO) 2018 stages IB2 through IVA, constitutes a considerable proportion of newly diagnosed cases in resource-limited settings (3). Concurrent chemoradiotherapy (CCRT) with platinum-based chemotherapy has been established as the standard therapeutic approach for LACC since 1999, demonstrating significant survival benefits in landmark randomized controlled trials (4). Despite advances in treatment delivery techniques including intensity-modulated radiotherapy and image-guided brachytherapy, approximately 30-40% of patients receiving CCRT experience treatment failure, manifesting as incomplete response, residual disease, or early recurrence within two years (5, 6). This substantial recurrence rate underscores the urgent need for reliable biomarkers capable of identifying high-risk patients who may benefit from treatment intensification or alternative therapeutic strategies.

Circulating tumor DNA (ctDNA) has emerged as a promising liquid biopsy approach for detecting molecular residual disease, monitoring tumor dynamics, and predicting clinical outcomes across diverse malignancies. In HPV-driven cancers, circulating HPV DNA represents a uniquely tumor-specific biomarker with exceptional analytical specificity, as integrated viral DNA sequences persist exclusively in malignant cells and are absent from normal tissues or high-grade precancerous lesions (7). Recent technological advances in droplet digital polymerase chain reaction (ddPCR) and next-generation sequencing (NGS) platforms enable highly sensitive quantification of HPV ctDNA, with analytical limits of detection approaching 5 copies per milliliter of plasma (8). Accumulating evidence from head and neck squamous cell carcinoma, anal carcinoma, and emerging cervical cancer cohorts demonstrates strong correlations between HPV ctDNA levels and tumor burden, treatment response kinetics, and disease recurrence risk (9, 10). Critically, persistent detectability of HPV ctDNA after chemoradiotherapy has been associated with dramatically inferior progression-free survival compared to molecular clearance, with hazard ratios exceeding 4.0 in multiple independent cohorts (11). A multicenter validation study reported 2-year PFS of 82% versus 15% for patients with undetectable versus detectable HPV ctDNA at 4–6 weeks post-CCRT (9). A meta-analysis encompassing 706 cervical cancer patients demonstrated that detectable ctDNA during treatment conferred substantially elevated risks for progression and mortality (12).

Despite these promising findings, prospective evidence evaluating HPV ctDNA as a dynamic biomarker specifically in LACC patients undergoing CCRT remains limited. Most existing studies are retrospective, utilize heterogeneous sampling schedules, employ non-standardized detection methodologies, or combine patients across diverse treatment paradigms, thereby constraining the generalizability and clinical applicability of findings (13–15). Besides, critical knowledge gaps persist regarding optimal timing of ctDNA assessments, prognostic thresholds for risk stratification, concordance with imaging-based response evaluation, and the independent predictive value of ctDNA status when adjusted for established clinicopathological risk factors. The present prospective cohort study aims to address these evidence gaps by evaluating whether dynamic monitoring of plasma HPV ctDNA can predict treatment response and prognosis in patients with LACC receiving standard CCRT.

## Methods and analysis

### Study design and patients

This prospective, single-center, observational cohort study will be conducted at the Department of Radiation Oncology, Tianjin Medical University Cancer Institute and Hospital, Tianjin, China, with patient recruitment planned to begin in January 2027 and continue for a 2-year period through December 2028. The hospital is a leading tertiary cancer center with advanced radiotherapy imaging facilities, enabling a multimodal image-guided radiotherapy system to improve target delineation and treatment planning, supporting high-quality clinical research. The study protocol was developed in accordance with the Declaration of Helsinki and adheres to the Standard Protocol Items: Recommendations for Interventional Trials (SPIRIT) guidelines for observational cohort studies. Ethical approval has been obtained from the Institutional Review Board of Tianjin Medical University Cancer Institute and Hospital (approval number: bc20254101). The study has been registered at ClinicalTrials.gov under the identifier of ChiCTR2600120726. All participants will provide written informed consent prior to enrollment. The overview of the study design and participant flow is illustrated in **Figure 1**.

**Figure 1 f1:**
[figure not shown]
Study flow diagram.

Eligible participants will be consecutively recruited from patients diagnosed with HPV-associated cervical cancer at our institution. Study-related examinations and blood sampling will be performed according to the protocol schedule outlined in **Table 1**. Importantly, this study does not involve investigational drugs or experimental interventions. All patients will receive standard-of-care CCRT according to National Comprehensive Cancer Network (NCCN) guidelines and Chinese Society of Clinical Oncology (CSCO) recommendations. No study medications will be provided free of charge, and no financial compensation or additional economic incentives will be offered to participants, treating physicians, or research staff for trial participation.

**Table 1 T1:** Schedule of enrolment, interventions, and assessments.

Study period	Enrolment	Allocation	Treatment & monitoring			Post-treatment follow-up		
Procedure/assessment	Screening (-t_1_)	Baseline (T0)	Week 3-4 (T1)	End CCRT (T2)	3 months (T3)	6 months	12 months	18–24 months
Enrolment								
Eligibility screening	X							
Informed consent	X							
Allocation		X						
Medical history	X							
Assessments								
Demographics/baseline	X	X						
Physical examination	X	X	X	X	X	X	X	X
ECOG performance status	X	X	X	X	X	X	X	X
Vital signs (BP HR T)	X	X	X	X	X	X	X	X
Concomitant medications	X	X	X	X	X	X	X	X
Laboratory tests	X	X		X	X	X	X	X
HPV DNA testing (cervical)	X							
Imaging								
Pelvic MRI	X	X			X	X	X	X
PET-CT (if indicated)	X				X	X	X	X
Treatment								
CCRT administration		X	X	X				
Treatment adherence		X	X	X				
Blood sampling								
Plasma HPV ctDNA		X	X	X	X	X	X	X
ctDNA analysis								
ddPCR (all samples)		X	X	X	X	X	X	X
NGS (subset)		X		X	X			
Response assessment								
RECIST 1.1 evaluation					X	X	X	X
Safety & qol								
Adverse event monitoring		X	X	X	X	X	X	X
EORTC QLQ-C30/CX24		X		X	X	X	X	X
Data management								
CRF completion	X	X	X	X	X	X	X	X
Data verification					X		X	X
Query resolution	Ongoing throughout study period							

BP, blood pressure; CCRT, concurrent chemoradiotherapy; CRF, case report form; ct, circulating tumor; ddPCR, droplet digital PCR; DNA, deoxyribonucleic acid; ECOG, Eastern Cooperative Oncology Group; EORTC, European Organization for Research and Treatment of Cancer; HPV, human papillomavirus; HR, heart rate; MRI, magnetic resonance imaging; NGS, next-generation sequencing; PET-CT, positron emission tomography-computed tomography; QLQ, Quality of Life Questionnaire; QOL, quality of life; RECIST, Response Evaluation Criteria in Solid Tumors; T, temperature.

The study team consists of gynecologic oncologists responsible for initial diagnosis and staging, radiation oncologists who will deliver CCRT and assess treatment response, medical oncologists who will manage chemotherapy administration, molecular laboratory specialists who will perform ctDNA analyses, biostatisticians who will conduct data analysis, and trained research nurses responsible for patient recruitment, blood sample collection and processing, data collection, and quality control monitoring.

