
### Clinical evaluation and imaging

Treatment response will be assessed at 3 months (± 2 weeks) after completion of CCRT using pelvic MRI as the primary imaging modality, supplemented by PET-CT in selected cases based on clinical indication (such as suspected distant metastases or equivocal MRI findings). MRI will be performed using a 1.5-Tesla or 3-Tesla scanner with appropriate pelvic coils, and will include multiparametric sequences such as T2-weighted imaging in axial, sagittal, and coronal planes, T1-weighted imaging, diffusion-weighted imaging (DWI) with apparent diffusion coefficient (ADC) mapping, and dynamic contrast-enhanced (DCE) imaging. Tumor response will be evaluated according to Response Evaluation Criteria in Solid Tumors (RECIST) version 1.1, with complete response (CR) defined as disappearance of all target lesions, partial response (PR) as at least a 30% decrease in the sum of diameters of target lesions, progressive disease (PD) as at least a 20% increase in the sum of diameters of target lesions or appearance of new lesions, and stable disease (SD) as neither sufficient shrinkage to qualify for PR nor sufficient increase to qualify for PD.

Follow-up imaging will be performed every 6 months (± 4 weeks) for the first 2 years, then annually for years 3–5, or more frequently if clinically indicated based on symptoms suggestive of disease recurrence (such as abnormal vaginal bleeding, pelvic pain, or new onset of symptoms). Additional imaging studies such as chest CT, abdominal CT, or bone scintigraphy may be performed at the discretion of the treating physician if metastatic disease is suspected. All imaging studies will be reviewed by radiologists with expertise in gynecologic oncology who are blinded to ctDNA results, and findings will be documented using standardized radiology report templates. Imaging-detected disease recurrence will be confirmed by biopsy whenever feasible and clinically appropriate to obtain histopathologic confirmation.

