Secondary outcome include: (1) Overall survival (OS), defined as the time from the initiation of CCRT to death from any cause, with patients who are alive at the time of analysis censored at the date they were last known to be alive; (2) Objective response rate (ORR), defined as the proportion of patients achieving CR or PR at the first imaging assessment (3 months post-CCRT) according to RECIST version 1.1 criteria; (3) Dynamic changes in plasma HPV ctDNA levels expressed as continuous variables (copies per mL) and categorical variables (detectable versus undetectable) at predefined time points (T0, T1, T2, T3, and follow-up time points) during and after CCRT, including assessment of ctDNA clearance kinetics (time to first undetectable ctDNA), nadir ctDNA levels, and patterns of ctDNA dynamics (rapid clearance, slow clearance, persistent detection, or reappearance after initial clearance); (4) Predictive performance of HPV ctDNA for disease recurrence, including calculation of sensitivity (proportion of patients with recurrence who have detectable ctDNA), specificity (proportion of patients without recurrence who have undetectable ctDNA), positive predictive value (PPV; probability of recurrence given detectable ctDNA), negative predictive value (NPV; probability of no recurrence given undetectable ctDNA), and area under the receiver operating characteristic curve (AUC-ROC) for ctDNA as a predictive biomarker, with 95% confidence intervals (CIs); and (5) Concordance between HPV ctDNA status and imaging-based assessment (MRI and/or PET-CT) in detecting residual disease at 3 months post-CCRT and early relapse during follow-up, assessed using Cohen’s kappa statistic and contingency table analysis. Additionally, we will explore the lead time advantage of ctDNA detection, defined as the time interval between ctDNA-detected recurrence and imaging-detected recurrence in patients who experience disease progression (20). The detailed schedule of assessments follows the SPIRIT framework and is presented in **Table 1**, which outlines all study procedures, evaluations, and time points from screening through close-out.

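### The exploratory lead time pools relapses inside and outside the only region imaged on schedule, so part of any ctDNA lead may reflect when the scan was done

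*Protocol article*

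**What the plan says.** **Imaging.** Clinical evaluation and imaging has the 3-month response assessed "using pelvic MRI as the primary imaging modality, supplemented by PET-CT in selected cases based on clinical indication", with examples of indication "such as suspected distant metastases or equivocal MRI findings". The text on later visits says "Follow-up imaging will be performed every 6 months (± 4 weeks) for the first 2 years" without naming a modality. Table 1 supplies it: pelvic MRI is marked without condition at 3, 6, 12 and 18–24 months, and the only other imaging row is conditional, "PET-CT (if indicated"). Chest CT, abdominal CT and bone scintigraphy "may be performed at the discretion of the treating physician if metastatic disease is suspected".

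**Blood.** The blood sampling section and Table 1 have plasma drawn from every patient at T0 to T3 and then at the follow-up visits. Routine sampling ends at progression. Extra samples are permitted, not required, when relapse is suspected.

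**Lead time.** Outcome measures introduces it as an additional exploration, "defined as the time interval between ctDNA-detected recurrence and imaging-detected recurrence in patients who experience disease progression". There is one definition for all progressors, with no split by site of relapse or by type of scan. Concordance at 3 months and during follow-up is a secondary outcome, measured by kappa against MRI and/or PET-CT.

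**The concern.** The two dates that make up the lead time do not arise in the same way for all relapses. In the pelvis, blood and MRI follow a calendar, and neither test has an advantage in timing. Outside the pelvis, the blood date still follows the calendar, but the imaging date waits until someone suspects metastasis or finds the MRI equivocal. The interval then contains the delay to suspicion as well as any biological lead.

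This does not depend on anyone knowing the ctDNA result. The radiologists are blinded and plasma is stored for batch analysis, yet the timing of the scan still follows suspicion.

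What is at stake is how the result is worded. The Abstract motivates the study by saying that current imaging-based assessment is "limited by delayed detection of treatment failure and poor sensitivity for microscopic residual disease". A positive pooled lead time would be read as support for that statement in general, although part of it may come only from the field and timing of the scans.

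**Working it through.** The plan states no figure for lead time, so there is none to reproduce. The check asks what lead a marker with **zero** true lead would show.

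**Inputs from the document.** Visits after CCRT are at 3, 6, 12, 18 and 24 months (Table 1, reading its last column as two visits) or at 3, 9, 15 and 21 months (sampling text, every 6 months after T3).

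**Assumptions not in the document.** The lesion becomes visible on a suitable scan at a time uniform between month 3 and the last visit. ctDNA becomes detectable at that same moment and is never missed. The scan for an extrapelvic lesion follows after an exponential delay with mean d = 2, 4 or 6 months. Between 30% and 60% of relapses are extrapelvic.

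**Pelvic relapse.** Blood and MRI are both positive at the next visit: lead = 0.

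**Extrapelvic relapse, negative leads recorded as zero.** If the wait to the next blood draw is uniform on (0, L), the mean lead is (d²/L)(1 − e^(−L/d)).

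- Text calendar, every L = 6:
  - d = 2: (4/6)(1 − e^(−3)) = 0.63
  - d = 4: (16/6)(1 − e^(−1.5)) = 2.07
  - d = 6: (36/6)(1 − e^(−1)) = 3.79
- Table 1 calendar, intervals 3, 6, 6, 6 (weight 3/21 on L = 3 and 18/21 on L = 6):
  - d = 2: (3 × 1.04 + 18 × 0.63)/21 = 0.69
  - d = 4 and d = 6, same formula: 2.18 and 3.93

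The share of extrapelvic relapses with a positive lead is the mean divided by d. It runs from 0.63/2 = 0.32 to 3.93/6 = 0.65.

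**Extrapelvic relapse, signed leads.** The mean is d minus the average wait, which is 3.00 months (text) or (3 × 1.5 + 18 × 3)/21 = 2.79 months (Table 1).

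| Mean delay d (months) | Negative leads set to 0 | Signed leads |
|---|---|---|
| 2 | 0.63 to 0.69 | −1.0 to −0.8 |
| 4 | 2.07 to 2.18 | +1.0 to +1.2 |
| 6 | 3.79 to 3.93 | +3.0 to +3.2 |

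**Pooled over all relapses, negative leads set to zero.** Extrapelvic share times the mean: from 0.3 × 0.63 = 0.2 to 0.6 × 3.93 = 2.4 months.

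**Second model.** With onset uniform over months 3 to 18 and blood always drawn at the suspicion visit, the pelvic lead is again 0. The extrapelvic lead is 1.2 to 1.4 months at a 3-month mean delay and 3.6 to 4.0 at 6 months.

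**Kappa at 3 months, error-free marker.** Let p be pelvic disease and e extrapelvic-only disease that was not scanned (both assumed). Observed agreement is 1 − e, and chance agreement is (p + e)p + (1 − p − e)(1 − p). Kappa is 0.86 for p/e = 0.20/0.05, 0.74 for 0.20/0.10, 0.74 for 0.15/0.08 and 0.58 for 0.15/0.15. Unscanned disease therefore **lowers** kappa.

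**The case against.** **The sign depends on how leads are recorded.** This is the strongest objection. With signed leads and a 2-month delay, the bias runs against ctDNA. The arithmetic is right, but routine sampling stops at progression. When imaging comes first there is usually no later ctDNA date, so the lead would be recorded as zero (if blood was drawn at suspicion) or be missing. As the plan is written, the bias favours ctDNA. Its lower end still rests on this.

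**The inputs are undocumented, and perfect detection is generous.** This stands. The article itself expects 30–40% of patients to be ctDNA-negative at baseline. Patients who do not shed ctDNA contribute no lead time, so the size is illustrative.

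**Lead over imaging as used in practice is a fair question.** This also stands. It calls for naming the comparator; it does not make the measure invalid.

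**Stronger readings that the document does not support.** A reader might infer that kappa at 3 months credits ctDNA for extrapelvic disease. It does the reverse: such a patient counts as ctDNA-positive and imaging-negative, which looks like a false positive. A reader might also infer that extrapelvic disease is never scanned. PET-CT and CT are allowed on indication, and every relapse with a lead time has an imaging date; the scan is late, not absent. Nor would computing kappa against pelvic MRI alone help, because the fall shown above is already the fall against pelvic-only imaging.

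**Conclusion.** The point holds for lead time. One pooled definition is applied to two kinds of imaging date, and for extrapelvic relapse a marker without any true lead can show a positive one. The size is about 0.6 to 3.9 months in extrapelvic relapses and 0.2 to 2.4 months pooled. This rests on assumed delays of 2 to 6 months, an assumed extrapelvic share of 30–60%, full detection, and negative leads not being recorded. The mechanism follows from the text; the size does not.

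For concordance, only a note is warranted: kappa at 3 months is lowered by extrapelvic disease that was not scanned, and patients differ in the imaging that they had.

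Lead time is exploratory and concordance secondary, and this point makes no claim about the primary comparison of PFS by ctDNA status. It is minor.

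**What to change.** In Outcome measures and Statistical analysis:

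- Report lead time separately for relapses first found within the field of the scheduled pelvic MRI and for those first found only outside it. Assign relapses found in both at once to the in-field group.
- Label the first as lead over scheduled pelvic MRI and the second as lead over suspicion-triggered imaging.
- Do not rest a general claim of earlier detection than imaging on the pooled figure.
- For concordance at 3 months, keep the planned comparator, state which imaging each patient had, and note that unscanned extrapelvic disease lowers kappa.

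This changes analysis and wording only; no scan is added, and the site of relapse should be available from the imaging reports. The cost is precision. The sample-size assumptions give a 2-year event rate of 0.3 × 0.50 + 0.7 × 0.25 = 0.325, so 48 to 57 patients yield 15.6 to 18.5 events, deaths included. At an assumed 30–60% extrapelvic share, that leaves at most about 6 to 13 in-field and 5 to 11 extrapelvic relapses, so both results would be descriptive.

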### Study sample and enrollment

#### Inclusion criteria

Participants will be eligible for inclusion if they meet all of the following criteria:

female patients aged 18–75 years;histologically confirmed cervical squamous cell carcinoma, adenocarcinoma, or adenosquamous carcinoma based on biopsy specimens reviewed by experienced pathologists;LACC staged as International Federation of Gynecology and Obstetrics (FIGO) 2018 classification stage IB2, IB3, II, III, or IVA, confirmed by clinical examination and imaging studies including pelvic magnetic resonance imaging (MRI) and/or positron emission tomography-computed tomography (PET-CT) (16);baseline confirmation of high-risk HPV infection (types 16 and 18) by quantitative HPV DNA testing performed on cervical tissue or liquid-based cytology samples using polymerase chain reaction (PCR)-based assays (17);planned to receive and medically able to complete definitive CCRT with curative intent;Eastern Cooperative Oncology Group (ECOG) performance status 0–1;adequate bone marrow function (white blood cell count ≥3.0×10^9^/L, absolute neutrophil count ≥1.5×10^9^/L, platelet count ≥100×10^9^/L, hemoglobin ≥90 g/L), adequate hepatic function (total bilirubin ≤1.5 times upper limit of normal [ULN], alanine aminotransferase and aspartate aminotransferase ≤2.5 times ULN), and adequate renal function (serum creatinine ≤1.5 times ULN or calculated creatinine clearance ≥60 mL/min);estimated life expectancy ≥6 months;ability to comply with the study protocol and scheduled follow-up visits and provision of written informed consent.

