#### Plasma HPV ctDNA detection by droplet digital PCR and exploratory NGS

ctDNA will be quantified using a validated multiplex ddPCR assay targeting the E6/E7 regions of HPV16 and HPV18, the two most common high-risk HPV types associated with cervical cancer. ddPCR provides absolute quantification without standard curves, offering high sensitivity and precision for low-abundance targets. All analyses will be performed at the Molecular Diagnostics Laboratory, Shanghai MedTech Bio-Molecular Testing Center, using the AccuONE-R300PB chip-based system with multiplex detection of HPV16, HPV18, and a human internal reference gene (ER) to ensure sample quality and normalize DNA input. Stringent quality control measures, including no-template and positive controls, will be applied, and samples failing QC or with insufficient droplet counts will be repeated. HPV ctDNA concentrations will be calculated as copies per milliliter of plasma. ctDNA positivity will be determined according to the prespecified analytical criteria of the validated ddPCR assay, including the limit of blank (LoB), limit of detection (LOD), limit of quantification (LOQ), droplet quality metrics, and negative and positive controls. Samples with HPV16/18 E6/E7 signals reaching or exceeding the assay-defined LOD/LOQ will be classified as ctDNA-positive/detectable, whereas samples with no HPV16/18 signal or signals not exceeding the LoB will be classified as ctDNA-negative/undetectable (18, 19). Trace-positive results will be defined as low-level HPV16/18 signals above the assay background or LoB but below the assay-defined LOD/LOQ, or as low-copy signals that do not meet the predefined criteria for reliable quantification (18). These samples will be repeated when sufficient residual cfDNA is available and will be reported separately. In the primary analysis, trace-positive samples will not be considered definitively ctDNA-positive. If trace-positive results are observed, an exploratory sensitivity analysis will be conducted by reclassifying these samples as ctDNA-positive to assess whether their classification affects the primary findings. Exploratory targeted NGS will be performed in approximately 20 patients to validate ddPCR findings and explore additional tumor-specific genomic alterations. Patients with detectable or trace-positive HPV ctDNA at 3 months after CCRT, disease recurrence or progression during follow-up, or high baseline ctDNA levels will be prioritized. Approximately one-third of the NGS subset will be selected from patients with undetectable ctDNA at 3 months, balanced by FIGO stage, histological subtype, and baseline HPV16/18 status. NGS findings will be exploratory and used for assay cross-validation and hypothesis generation rather than formal subgroup inference. Detailed procedures for cfDNA extraction, assay setup, primer/probe sequences, thermal cycling, quality control, quantification formulas, and NGS methods are provided in the Supplementary Materials.

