### Statistical analysis

All statistical analyses will be performed using SPSS v27.0 (IBM Corp., USA) and R v4.3.0 or later. Baseline characteristics will be summarized using descriptive statistics: continuous variables as mean ± SD or median (IQR) depending on normality, and categorical variables as frequencies and percentages. Group comparisons (ctDNA-positive vs ctDNA-negative) will use Student’s t-test or Mann-Whitney U test for continuous variables, and χ² or Fisher’s exact test for categorical variables.

Longitudinal ctDNA changes will be analyzed using generalized estimating equations (GEE) or linear mixed-effects models to account for repeated measures, adjusted for baseline covariates such as FIGO stage, tumor size, and nodal status. PFS and OS will be estimated by Kaplan-Meier method and compared with log-rank tests; hazard ratios (HRs) with 95% CIs will be obtained from univariate and multivariate Cox proportional hazards models. Covariates in multivariate models will be checked for collinearity (VIF >5) and proportional hazards assumption (Schoenfeld residuals).

Predictive performance of ctDNA for recurrence will be evaluated using ROC curves (AUC, sensitivity, specificity, PPV, NPV); optimal cut-offs for continuous ctDNA will be determined via Youden’s index. Concordance between ctDNA and imaging will be assessed with Cohen’s kappa. Missing data<20% will be handled by multiple imputation (MICE), with sensitivity analyses including complete-case analyses. Patients lost to follow-up will be censored at the last known date. Two-sided p-values<0.05 indicate statistical significance, with multiple testing correction applied for secondary endpoints. Exploratory subgroup analyses may be conducted by FIGO stage, histology, or baseline HPV type. These subgroup analyses will be exploratory and hypothesis-generating and will not be used for confirmatory subgroup inference.

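### The HPV entry criterion is loosely worded and accepts a cytology result that does not tie HPV16/18 to the tumour, so a few tumours invisible to the assay could be counted as ctDNA-undetectable

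*Protocol article*

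**What the plan says.** The operative rule is in the protocol article, Inclusion criteria: "baseline confirmation of high-risk HPV infection (types 16 and 18) by quantitative HPV DNA testing performed on cervical tissue or liquid-based cytology samples". The abstract (Methods/design) asks for "histologically confirmed LACC (FIGO 2018 stage IB2–IVA) and baseline high-risk HPV infection" and names no types. Under Study design and patients, participants are to be "consecutively recruited from patients diagnosed with HPV-associated cervical cancer at our institution", again without types. Table 1 lists one cervical HPV DNA test, at screening.

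The section on plasma detection describes a "validated multiplex ddPCR assay targeting the E6/E7 regions of HPV16 and HPV18". Its classification rule has two main branches: "Samples with HPV16/18 E6/E7 signals reaching or exceeding the assay-defined LOD/LOQ will be classified as ctDNA-positive/detectable", while "samples with no HPV16/18 signal or signals not exceeding the LoB will be classified as ctDNA-negative/undetectable". Trace signals are handled separately. There is no category for a patient whose tumour the assay could not be expected to see, and a plasma signal is not matched to the type found at entry.

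HPV type is used again in two places. The NGS subset is to be balanced by baseline HPV16/18 status, and under Statistical analysis "Exploratory subgroup analyses may be conducted by FIGO stage, histology, or baseline HPV type".

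**The concern.** There are two separate weaknesses.

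The first is wording. An eligibility criterion should not need interpretation, yet this one literally demands co-infection with both types, and the two shorter descriptions elsewhere could lead a screener to think that any high-risk type will do.

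The second is the specimen. The scientific case for the marker, made in the Introduction, is that viral sequences belong to the malignant cells. A liquid-based cytology result establishes infection of the cervix, and nothing in the entry procedure links the detected type to the tumour. If the tumour is driven by a type outside the assay's two targets, plasma should stay negative whatever residual disease is present. Her later progression would then be recorded in the undetectable group. That affects the primary comparison at 3 months (T3), and it counts as a missed recurrence in sensitivity and in negative predictive value.

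**Working it through.** **Reading the passages together.** If both types were required, every patient would have the same HPV type status. The subgroup by HPV type and the NGS balancing would then have nothing to compare. Both make sense only if either type qualifies, so either type is the intended meaning. On that reading a patient with only another high-risk type is ineligible. What remains is the patient who is 16/18-positive on cytology with a tumour driven by another type.

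**Reproducing the plan's figures** (Sample size calculation: 2-year PFS 50% if ctDNA-positive and 75% if negative, 30% positive at T3, two-sided 0.05, 80% power, 15% attrition):

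- HR = ln(0.50)/ln(0.75) = 0.6931/0.2877 = 2.41, as stated.
- (1.96 + 0.842)² / [(ln 2.41)² × 0.30 × 0.70] = 7.851/0.1625 = 48.3, against a stated 48.
- 48/0.85 = 56.5, so 57, as stated.

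**Illustrating the dilution.** Let f be the share of patients whose tumour the assay cannot see. This is my assumption; the document gives no value. Suppose these patients have the overall 2-year PFS, 0.30 × 0.50 + 0.70 × 0.75 = 0.675, and all are classed as undetectable. Then:

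- observed positive share p = 0.30(1 − f)
- undetectable-group PFS = [0.70(1 − f) × 0.75 + f × 0.675]/(1 − p)
- HR = ln(0.50)/ln(undetectable-group PFS)
- sensitivity = 0.50p/0.325, taking failure by 2 years (1 − 0.675 = 0.325) as recurrence
- negative predictive value = undetectable-group PFS, on the same footing

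For f = 5%: p = 0.285; PFS = (0.49875 + 0.03375)/0.715 = 0.745; HR = 2.35; sensitivity = 0.1425/0.325.
For f = 10%: p = 0.27; PFS = (0.4725 + 0.0675)/0.73 = 0.740; HR = 2.30; sensitivity = 0.135/0.325.

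| f (assumed) | T3-positive | PFS if undetectable (= NPV) | HR | Sensitivity |
|---|---|---|---|---|
| 0% | 30.0% | 75.0% | 2.41 | 46.2% |
| 5% | 28.5% | 74.5% | 2.35 | 43.8% |
| 10% | 27.0% | 74.0% | 2.30 | 41.5% |

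The direction depends on the unseen patients doing worse than the 75% assumed for the undetectable group. Average prognosis satisfies that.

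**The case against.** The strongest reply is that there is no real conflict. The inclusion criteria are the operative text and name the same two types that the assay measures. The abstract is only shorter, and the recruitment sentence describes the source population. This stands. A reader might infer that the protocol admits any high-risk type, or that it requires co-infection with both; the document supports neither.

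A second reply is that the remaining route is narrow and has no frequency attached. This also stands. A reader might put larger shares, such as 10% to 30%, into the sample-size formula and conclude that the trial needs many more patients. The document gives no basis for such shares. The assumed 30% positivity and 75% PFS may already include tumours that the assay misses, so the loss could be counted twice. The formula also returns a number of events, so its output should not be read as an enrolment figure.

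A third reply is that Feasibility and limitation already acknowledges negative plasma at baseline in about 30-40% of patients and lists genotype distribution and assay design among possible causes. That is fair, and low shedding is probably the larger route. But the acknowledgement does not change who is counted as undetectable. It also speaks of tumours confirmed as HPV-positive, which the entry rule does not demand of a patient typed on cytology. The NGS work does not close the gap: it covers about 20 patients, about one-third of them undetectable at 3 months, and is exploratory.

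Finally, if incidental cervical virus did reach plasma, such a patient could test positive, so it would be too strong to say that she never can. On the protocol's own premise of tumour specificity this should be uncommon. That is why separate reporting of an unmatched type is enough.

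**Conclusion.** The point holds in a limited form. The criterion needs a wording correction, and accepting cytology leaves a small opening through which a patient with no measurable tumour marker can be enrolled and counted as ctDNA-undetectable. The expected effect is attenuation of the primary hazard ratio, with lower sensitivity and negative predictive value. Its size cannot be determined from the document. The illustrated fall from 2.41 to about 2.35 at a 5% share, or about 2.30 at 10%, rests on the protocol's planning assumptions, on average prognosis for the unseen patients, and on planning figures that do not already include them. The true share may be below 5%. This does not justify a new sample size. It does justify a correction before recruitment, planned for January 2027, because the cost is low.

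**What to change.** 1. In the inclusion criteria, write HPV16 and/or HPV18, and use the same wording in the abstract and the recruitment paragraph.
2. Do the entry typing on the diagnostic biopsy where material is available. Tissue is already an allowed specimen, and a biopsy is already needed for histology.
3. Record the specimen used. Flag patients typed on cytology only, and repeat the primary T3 comparison without them as a sensitivity analysis.
4. Report separately any plasma signal of a type not found at entry.
5. Prespecify a sensitivity analysis of the T3 comparison restricted to patients with detectable ctDNA at baseline (T0). That plasma is already collected from everyone, and this analysis covers both the genotype route and the larger low-shedding route.

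The cost is protocol wording and PCR on existing tissue. The sensitivity analyses use fewer patients. With 30-40% negative at baseline, the T0-detectable set would be about 34 to 40 of 57 before attrition (57 × 0.60 = 34.2; 57 × 0.70 = 39.9), so it should support the primary result and not replace it. The number typed on cytology only is not known in advance.
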